## **8.3 Handling of Safety Parameters**

### **8.3.1 Serious Adverse Events**

The ICH Guideline for Clinical Safety Data Management, Definitions and Standards for Expedited Reporting will be followed. A serious adverse event (SAE) includes any experience which :

- Is fatal
- Is life-threatening
- Requires in-patient hospitalisation
- Results in persistent or significant disability/incapacity

- Is medically significant or requires intervention to prevent one or other of the outcomes listed above

For all adverse events the relationship to the study drug, action taken regarding study drug, and outcome to date will be recorded on the AE form of the CRF.

### **8.3.2 Serious Adverse Event Reporting**

Suspected unexpected serious adverse reactions (SUSARs) will be faxed using the standard CIOMS form (including the EudraCT number of the study) within 24 hours of the study site learning of the event to the Norwegian MA and the drug manufacturer, Asta Medica, Frankfurt, Germany.

### **8.3.3 Treatment and Follow-up of Adverse Events**

AEs should be followed up until they have returned to baseline or stabilised. If the AE has a clear explanation, this should be recorded on the AE in the CRF. Treatment of AEs should follow normal medical standards of care.

### **8.3.4 Follow-up of Abnormal Laboratory Test Values**

If laboratory tests are abnormal and clinically significant as described in 8.2, the tests should be repeated immediately and followed up until they have returned to the normal range and/or an adequate explanation has been found. In the event of an adequate explanation, this should be recorded in the CRF.

## **8.4 Discontinuation Criteria**

A patient should be withdrawn from trial treatment at any time if, in the opinion of the investigator, it is medically necessary, or if it is the wish of the patient. Patients may

withdraw at their own request at any time during the trial period. Should a patient make such a request, the reason should be recorded in the CRF and final visit examinations be performed before addition of new therapy. If a medicine, which is not allowed in the trial, is needed, patients must be withdrawn from the trial. If concomitant therapy needs to be changed in the opinion of the consultant rheumatologist, the patient will be withdrawn from the trial. The consultant rheumatologist, in consultation with the patient, will decide the future course of treatment.

## **9 STATISTICS**

### **9.1 Sample Size**

Assuming a difference of 0.6 unit reduction from baseline in mean DAS28 score on cetorelix compared with placebo and an underlying standard deviation for the changes from baseline of 1.0 unit (from previous data), we calculated that

$$N = 2(Z_{\alpha} + Z_{\beta})^2 \sigma^2 / \delta^2,$$

where  $\delta = \mu_2 - \mu_1 = 0.6$

$$N = 2 (1.96 + 0.842)^2 1^2 / 0.6^2$$

**N= 44** per treatment group

To allow for drop-outs, **49 patients in each group** were considered adequate. The significance is 0.05 (two-tailed) with a power of 0.8.

### **9.2 Analysis Populations**

#### **9.2.1 Safety Population**

This population will be used for all summaries of safety data (i.e. adverse events, concomitant medications, concomitant diseases, and laboratory data). The safety

population will include all patients who are randomised and received any injections of study drug.

### **9.2.2 Intention to Treat (ITT) Population**

This population will be used for all efficacy analyses. All randomised patients who have received any injections of study drug will be included in this population.

### **9.2.3 Per Protocol Population**

The per-protocol population will be used only for the analysis of the primary endpoint as a sensitivity check to the ITT analysis, and in order to evaluate the influence of major protocol violations and protocol deviators. Patients may be excluded if they significantly violate the inclusion/exclusion criteria or deviate from the study plan.

Patients who receive incorrect therapy from that intended will be excluded from the per-protocol population.

## **9.3 Statistical and Analysis Methods**

The study period is 15 days and the statistical analyses will be performed on the data collected up to this point. Once all patients have completed the trial, a database lock will occur. Treatment assignments will be primarily unblinded for the study statistician for the purpose of data analysis.

All analyses, summaries and listings will be performed using statistical software, including Stata 11 (StatCorp LP, College Station, TX) and StatXact 9 (Cytel Inc., Cambridge, MA). For both intervention arms, means and their corresponding standard deviations (SD) will be computed to describe the distributions of demographic and

baseline variables. Means and SDs will also be used to describe distributions of corresponding changes from baseline. Distributions for categorical variables will be described for each group with frequencies and/or percentages. Medians and quartiles will describe percent changes. Two-sided tests and confidence intervals will be used at all end points. Because of the unpredictability of some of the problems that may arise with regards to data collection, detailed consideration of the handling of unforeseen irregularities (e.g. outliers) will be deferred until blind review of the data at the end of the trial.

### **9.3.1 Assessment of Treatment Response**

Based on VAS, HAQ, ESR, CRP, and Joint Count Scores, a number of disease activity scores (DAS28, EULAR response, ACR 20/50/70/90 response) will be calculated for each visit and used for the assessments of treatment response.

*DAS28CRP:*

See earlier for calculation of this

*ACR definition of improvement:*

‘ACR20’, ‘ACR50’, ‘ACR70’, and ‘ACR90’ are defined as 20%, 50%, 70%, and 90% improvement from baseline, respectively, in:

- Tender Joint Count (TJC) and
- Swollen Joint Count (SJC) and

and in 3 of the following 5 assessments:

- Patient Pain Assessment (VAS Pain)
- Patient Global Assessment (VAS Global)

- Physician Global Assessment (VAS Physician)
- Patient Self-Assessed Disability (HAQ)
- Acute Phase Reactant (CRP or ESR)

*EULAR response criteria:*

The EULAR response criteria are based on attained level and change in DAS, classifying patients as good, moderate or non responders, as follows:

| DAS28 at
endpoint | Improvement in DAS28 from baseline |                     |            |
|----------------------|------------------------------------|---------------------|------------|
|                      | >1.2                               | >0.6 and $\leq 1.2$ | $\leq 0.6$ |
| $\leq 3.2$           | Good                               | Moderate            | None       |
| > 3.2 and $\leq 5.1$ | Moderate                           | Moderate            | None       |
| >5.1                 | Moderate                           | None                | None       |

The presence of ‘good’, ‘moderate’ or ‘no response’ will be determined for each visit.

Hypothesis testing

The cetrotide arm will be considered superior to placebo if there is enough statistical evidence to reject the following null hypothesis:

Ho:  $\mu_1 = \mu_2$  (i.e. adjusted change in DAS28CRP scores in the cetrotide and placebo arms are equal),

and accept the alternative hypothesis:

Ho:  $\mu_1 \neq \mu_2$  (i.e. the adjusted change in DAS28CRP score in the cetrotide arm is superior to the change in DAS28 score in the placebo arm).

If the test result is statistically significant at  $\alpha=0.05$  level, we will conclude that the cetrotide arm demonstrated a superior change in DAS28CRP score at day 5b when compared to placebo.

### **9.3.2 Primary Endpoint and Analysis**

Cetrorelix has a rapid onset and offset effect; therefore we have chosen an early primary endpoint. The primary endpoint is the change in disease activity score (DAS28CRP) on Day 5b (12 hours after the last injection [time point when LH and FSH levels are expected to be lowest]).

The primary variable will be analysed by ANCOVA, linear regression with last measurement (in this case day 5b) as the dependent variable and treatment and baseline measurement as independent variables (covariates).

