#### **4.2 Number of Patients/Assignments to Treatment Groups**

98 patients will be recruited into this study and will be randomised equally into the 2 intervention groups. Patients will be stratified by sex to avoid any random gender bias between the two groups. There will be no replacement of patients should a patient's treatment be discontinued for any reason.

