#### **4.3 Patient Randomisation and Enrolment**

Patients will be evaluated for eligibility to ensure the criteria in section 5.2 and 5.3 are filled. All patients must sign the Informed Consent form prior to screening. A screening form will be filled for each patient. Eligible patients will be randomised, through computer generated allocation, prior to receiving any study medication; this is carried out by study personnel who are not involved with outcome assessments. Randomisation

will be carried out in dynamic blocks (varying block sizes unknown to the study site), and stratified for sex. Once a patient has been through the screening process and has given informed consent for participation, the research nurse obtains randomisation information by calling an offsite central office. The patient will be provided with a unique medication number and randomisation number. As confirmation, the investigator will be provided with a posted verification of each patient's registration.

A patient's treatment assignment should only be unblinded when knowledge of the treatment is essential for the further management of the patient.

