### **9.3.3 Secondary Endpoints and Analysis**

**DAS28 refers to both DAS28ESR and DAS28CRP**

#### **Secondary Endpoints:**

1. Change in DAS28 levels from baseline to days 2, 10, and 15 will be analyzed using ANCOVA (see section 9.3.2).
2. The change in cytokine levels, cardiovascular markers, endothelial function markers and bone markers from baseline to day 2, 5, 10 and 15 will be analyzed using ANCOVA in a similar manner as the DAS28 levels (see section 9.3.2).
3. The change in ACR core set measures from baseline to day 2, 5, 10 and 15 will be analyzed using ANCOVA in a similar manner as the DAS28 levels (see section 9.3.2).

4. The proportion of patients with ACR20/50/70/(90) response on day 2, 5, 10 and 15 will be analyzed using the Pearson's  $\chi^2$  test (or Suissa Shuster exact unconditional test)
5. The proportion of patients with EULAR response rate ('Good', 'Moderate' or 'None') from baseline to day 2, 5, 10 and 15. The Pearson's  $\chi^2$  test for trend for comparisons of proportions among ordered groups (or Suissa Shuster exact unconditional test) will be used to assess the difference in proportions between groups.
6. DAS28CRP low disease activity on day 2, 5, 10 and 15 (defined as DAS28  $\leq 3.2$ ) will be analyzed using the Pearson's  $\chi^2$  test (or Suissa Shuster exact unconditional test)
7. DAS28CRP remission on day 2, 5, 10 and 15 (defined as DAS28  $< 2.6$ ) will be analyzed using the Pearson's  $\chi^2$  test (or Suissa Shuster exact unconditional test)
8. The correlation between relative changes in hormones, disease activity and biomarkers will be assessed using the Spearman rank correlation.
9. The change in HAQ scores from baseline to day 5, 10 and 15 will be analyzed using ANCOVA in a similar manner as the DAS28 levels (see section 9.3.2).
10. The change in anti-CCP levels from baseline to day 2, 5, 10 and 15 will be analyzed using ANCOVA in a similar manner as the DAS28 levels (see section 9.3.2).
11. Number of patients with AEs (and SAEs) up to day 15 in each group will be analyzed using the Pearson's  $\chi^2$  test (or Suissa Shuster exact unconditional test)

The variables described in the secondary endpoints are highly correlated and therefore no adjustment has been made for multiple testing.

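### Randomisation is stratified by sex, but the primary ANCOVA and the continuous secondary analyses adjust only for baseline; to the extent that sex predicts outcome, the test is slightly conservative and a little power is lost

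*Protocol*

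**What the plan says.** **Design.** Section 4.2 states: "Patients will be stratified by sex to avoid any random gender bias between the two groups". Section 4.3 adds that randomisation "will be carried out in dynamic blocks (varying block sizes unknown to the study site), and stratified for sex". No other stratification factor is named.

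**Primary analysis.** Section 9.3.2 specifies a linear regression with the day 5b measurement "as the dependent variable and treatment and baseline measurement as independent variables (covariates". The list is complete as written, and sex is not on it.

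**Secondary analyses.** In section 9.3.3, items 1, 2, 3, 9 and 10 (DAS28 on other days, biomarkers, ACR core measures, HAQ, anti-CCP) refer back to that ANCOVA. The response endpoints are tested without strata. Item 4 reads "The proportion of patients with ACR20/50/70/(90) response on day 2, 5, 10 and 15 will be analyzed using the Pearson's" chi-square (or the Suissa-Shuster test), items 6 and 7 do the same for low disease activity and remission, and EULAR response gets a chi-square "test for trend for comparisons of proportions among ordered groups (or Suissa Shuster exact unconditional test").

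**Elsewhere.** The hypothesis text in section 9.3.1 speaks of an adjusted change, but the only adjustment defined is for baseline. The text on appropriateness of methods, after 9.3.3, allows transformations and nonparametric alternatives and does not add sex. After randomisation, sex reappears only in the presentation of adverse events (section 8.1).

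**The concern.** Blocked allocation within each sex keeps the arms nearly balanced on sex, so differences between the sexes contribute almost nothing to the sampling variation of the treatment difference. A model without sex still leaves those differences in the residual. The reported standard error then describes a trial in which sex could have been unbalanced by chance, which is not the trial being run.

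If sex predicts day 5b DAS28CRP given baseline, three things follow: confidence intervals are wider than they need be, the true type I error is below 0.05, and part of the precision bought by stratifying is not used. This matters somewhat in a trial planned at 80% power with no replacement of patients. The protocol writes the model out, so this is a stated choice and not a detail left for a later document.

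**Working it through.** **Inputs from the protocol.** Section 9.1: "Assuming a difference of 0.6 unit reduction from baseline in mean DAS28 score on cetorelix compared with placebo", SD of change 1.0, and "The significance is 0.05 (two-tailed) with a power of 0.8". The result is 44 per arm, raised to 49 for drop-outs (98 in total).

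**Inputs that are assumptions.** The share R² of residual variance explained by sex given treatment and baseline is not in the documents; I use 2%, 5% and 10%. I take the protocol's SD of 1.0 as the residual SD of the model without sex.

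**Step 1: the plan's own figure.** N = 2(1.96 + 0.842)² × 1² / 0.6² = 43.6, rounded up to 44. This reproduces. Forty-four of 49 corresponds to about 10% drop-out.

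**Step 2: formulas.** Let z = 0.6/√(2/44) = 0.6/0.2132 = 2.814. Under allocation balanced on sex, the true standard error is √(1 − R²) times the one reported without sex. Hence:

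- type I error without sex = 2[1 − Φ(1.96/√(1 − R²))]
- power without sex = Φ((z − 1.96)/√(1 − R²))
- power with sex = Φ(z/√(1 − R²) − 1.96)

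For example, at R² = 10%, √0.90 = 0.949. Type I error is 2[1 − Φ(2.066)] = 3.9%, power without sex is Φ(0.900) = 81.6%, and power with sex is Φ(1.006) = 84.3%.

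**Step 3: results at 44 per arm.**

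| R² (assumed) | Type I error without sex | Power without sex | Power with sex | Gain (points) |
|---|---|---|---|---|
| 0 | 5.0% | 80.4% | 80.4% | 0 |
| 2% | 4.8% | 80.6% | 81.1% | 0.5 |
| 5% | 4.4% | 81.0% | 82.3% | 1.3 |
| 10% | 3.9% | 81.6% | 84.3% | 2.7 |

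At 49 per arm, z = 2.970 and the gains are 0.5, 1.2 and 2.3 points.

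**Step 4: what these R² values mean.** With a sex difference g in DAS28 units given baseline, a share p of men and SD 1.0, R² = g²p(1 − p). At p = 0.3, R² of 2% needs g = √(0.02/0.21) = 0.31, and 10% needs g = √(0.10/0.21) = 0.69.

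**Step 5: simulation check.** Stratified blocks of 4 and 6, 98 patients, 30% men (assumed), 10,000 trials per scenario:

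| g | Type I error without / with sex | Power without / with sex |
|---|---|---|
| 0 | 0.048 / 0.048 | 0.835 / 0.835 |
| 0.4 | 0.046 / 0.048 | 0.840 / 0.849 |
| 0.8 | 0.034 / 0.052 | 0.848 / 0.884 |

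At g = 0.8 the mean reported standard error without sex was 0.203, against an actual SD of the estimate of 0.190. With sex in the model the reported value was 0.189.

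**Step 6: binary endpoints.** Chi-square against sex-stratified Mantel-Haenszel, with an assumed 20% control response in women, treatment odds ratio 3.3, 98 patients, 30% men and 8,000 trials per scenario:

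| Sex odds ratio | Type I error, chi-square / MH | Power, chi-square / MH |
|---|---|---|
| 1 | 0.055 / 0.052 | 0.772 / 0.771 |
| 2 | 0.050 / 0.051 | 0.780 / 0.785 |
| 4 | 0.041 / 0.052 | 0.767 / 0.786 |

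The chi-square test becomes conservative only at the strongest sex effect tried, and the power gain is at most about 2 points.

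**The case against.** The strongest reply is that nothing is lost unless sex predicts the outcome after baseline adjustment. Baseline DAS28CRP is already in the model and should absorb much of any sex difference in disease level. The documents report no residual sex effect; section 4.2 gives only the aim of avoiding chance imbalance. The upper end of the range is also generous: 10% of residual variance needs a sex difference of at least √(0.10/0.25) = 0.63 units at any sex ratio. That exceeds the planned treatment effect of 0.6 and would have to arise within five days. Any error is on the safe side, in a proof-of-concept trial. All of this stands, and it limits the point to a modest, conditional gain in precision. It does not defend leaving the stratum out, because including it costs practically nothing even when sex has no effect.

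A second reply is that the response-rate tests are hardly affected. This also stands. The simulation shows no conservatism at sex odds ratios of 1 and 2.

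A reader might also infer that low disease activity and remission need a logistic model on baseline DAS28CRP, because eligibility is set at screening, up to 28 days before dosing, and some patients may be at or below 3.2 at baseline. That does not follow from the stratification. Randomisation makes it a question of precision, not bias. Such a model would replace a comparison of proportions with a conditional odds ratio, and it could be unstable if few of 98 patients reach remission. It is not part of this point.

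**Conclusion.** The mismatch between design and analysis is plain in the text and worth correcting. Its effect is conditional and modest: for an assumed 2% to 10% of residual variance due to sex, type I error is about 4.8% to 3.9%, and 0.5 to 2.7 power points are forgone at 44 per arm (0.5 to 2.3 at 49). At zero sex effect the loss is nil.

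A reader might infer that the standard errors are definitely too large and that every test in the plan is conservative. The documents do not support this. They give neither the sex effect nor the sex ratio, and the binary tests are little affected. Nor does the omission undermine the primary test or the sample size: the estimate is unbiased, a positive result is not inflated, and the planned 44 per arm reproduces. This is a recommended improvement, not a flaw that invalidates the analysis.

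**What to change.** In section 9.3.2, name the independent variables as treatment, baseline value and sex (randomisation stratum). State in section 9.3.3 that the same model applies to every ANCOVA there. Make the change before unblinding.

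Optionally, use a Mantel-Haenszel test stratified by sex for the binary response endpoints (ACR response, low disease activity, remission), where the expected gain is about 0 to 2 points. The exact unconditional alternative and the check of expected cell frequencies can stay for sparse tables.

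The cost is a short wording change and one degree of freedom out of about 95 (98 patients less intercept, treatment and baseline). Sex is already recorded for randomisation, so no new data are needed.

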### **9.3.3 Secondary Endpoints and Analysis**

**DAS28 refers to both DAS28ESR and DAS28CRP**

#### **Secondary Endpoints:**

1. Change in DAS28 levels from baseline to days 2, 10, and 15 will be analyzed using ANCOVA (see section 9.3.2).
2. The change in cytokine levels, cardiovascular markers, endothelial function markers and bone markers from baseline to day 2, 5, 10 and 15 will be analyzed using ANCOVA in a similar manner as the DAS28 levels (see section 9.3.2).
3. The change in ACR core set measures from baseline to day 2, 5, 10 and 15 will be analyzed using ANCOVA in a similar manner as the DAS28 levels (see section 9.3.2).

4. The proportion of patients with ACR20/50/70/(90) response on day 2, 5, 10 and 15 will be analyzed using the Pearson's  $\chi^2$  test (or Suissa Shuster exact unconditional test)
5. The proportion of patients with EULAR response rate ('Good', 'Moderate' or 'None') from baseline to day 2, 5, 10 and 15. The Pearson's  $\chi^2$  test for trend for comparisons of proportions among ordered groups (or Suissa Shuster exact unconditional test) will be used to assess the difference in proportions between groups.
6. DAS28CRP low disease activity on day 2, 5, 10 and 15 (defined as DAS28  $\leq 3.2$ ) will be analyzed using the Pearson's  $\chi^2$  test (or Suissa Shuster exact unconditional test)
7. DAS28CRP remission on day 2, 5, 10 and 15 (defined as DAS28  $< 2.6$ ) will be analyzed using the Pearson's  $\chi^2$  test (or Suissa Shuster exact unconditional test)
8. The correlation between relative changes in hormones, disease activity and biomarkers will be assessed using the Spearman rank correlation.
9. The change in HAQ scores from baseline to day 5, 10 and 15 will be analyzed using ANCOVA in a similar manner as the DAS28 levels (see section 9.3.2).
10. The change in anti-CCP levels from baseline to day 2, 5, 10 and 15 will be analyzed using ANCOVA in a similar manner as the DAS28 levels (see section 9.3.2).
11. Number of patients with AEs (and SAEs) up to day 15 in each group will be analyzed using the Pearson's  $\chi^2$  test (or Suissa Shuster exact unconditional test)

The variables described in the secondary endpoints are highly correlated and therefore no adjustment has been made for multiple testing.

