**Figure 1**

| Visit                                  | 0              | 1             | 2 | 3 | 4 |
|-----------------------------------------------|-----------------------|----------------------|----------|----------|----------|
| Day                                    | -28
screen | 1
(BL+R)* | 2 | 3 | 4 |
| Inclusion/Exclusion                           | X                     |                      |          |          |          |
| Demographics                                  | X                     |                      |          |          |          |
| Signed Informed
Consent                    | X                     |                      |          |          |          |
| Medical History                               | X                     |                      |          |          |          |
| Vital Signs                                   | X                     | X                    | X        | X        | X        |
| Physical Exam                                 | X                     |                      |          |          |          |
| DAS28 (with 66/68)
Assessment              | X                     | X                    | X        | X        | X        |
| VAS (pain, global
patient/physician)       | X                     | X                    | X        | X        | X        |
| HAQ                                           |                       | X                    |          |          |          |
| Pregnancy Test a                   | X                     |                      |          |          |          |
| Rheumatoid Factor                             | X                     | X                    | X        |          |          |
| Anti-CCP                                      | X                     | X                    | X        |          |          |
| CRP/ESR                                       | X                     | X                    | X        |          |          |
| Haematology/Chemistry
Freeze blood samples | X                     | X                    | X        |          |          |
| Urinanalysis (dipstick)                       | X                     | X                    | X        |          |          |
| Cetrotide/Placebo
Administration           |                       | X                    | X        | X        | X        |

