## **6.7 Study Assessments**

Complete efficacy and safety assessments will be made on Days 1 (baseline), 2, 5b, 10, and 15.

The sequence of assessments will be as follows:

1. Patient reported assessments: patient's global assessment of disease activity (VAS), pain (VAS), HAQ
2. Other efficacy assessments: joint counts, physicians global assessment of disease activity
3. Safety assessments
4. Laboratory samples for safety and efficacy will be obtained as in Figure 1

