### **6.7.1 Clinical Assessments**

The outcome assessor, who is blinded to treatment group, will perform joint assessments at all visits. All joint assessments in the individual patients are planned to be performed by the same assessor. The following assessments will be performed according to the schedule in Figure 1.

- *Patient/Physician assessment of global disease activity:* The patient/physician will indicate their overall ('global') assessment of disease activity on a horizontal VAS (0-100 mm). The scale ranges from 'very well' to 'very poorly'.
- *Patients' assessment of pain (on a Visual Analogue Scale (VAS)):* On a horizontal VAS (0-100 mm), the patients will indicate their current level of pain. The left end (0 mm) signifies no pain and the right end (100 mm) signifies the most pain possible.
- *Patient self-assessed disability (Health Assessment Questionnaire (HAQ)-score):*

- The functional status of the patient will be assessed by means of the disability index of the HAQ. This 20-question instrument assesses the degree of difficulty a person has in accomplishing tasks in 8 functional areas (dressing, arising, eating, walking, hygiene, reaching, gripping and errands/chores). Responses in each functional area are scored from 0 indicating no difficulty, to 3, indicating inability to perform a task in that area. The mean value is reported.
- *Swollen Joint Count/Tender Joint Count*: An assessment of 28 joints for swelling and tenderness will be made. Joints will be assessed and noted as swollen/not swollen and tender/not tender by pressure and joint manipulation on physical examination. Joints which have been replaced, fused, undergone synovectomy at any time point prior to the study will be documented as non evaluable- NE.
- *Duration of morning stiffness*: The duration of morning stiffness at the morning of each visit will be assessed in minutes.

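### Figure 1 and item 9 omit the day 2 HAQ that section 6.7 and the day 2 ACR analyses call for, and the joint count behind ACR response (28 or 66/68) is not fixed

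*Protocol*

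**What the plan says.** **ACR analyses on day 2.** Protocol section 9.3.3, item 3, plans "The change in ACR core set measures from baseline to day 2, 5, 10 and 15", and item 4 plans "The proportion of patients with ACR20/50/70/(90) response on day 2, 5, 10 and 15". Section 9.3.1 defines response as the stated percentage improvement in tender and swollen joint counts "and in 3 of the following 5 assessments". The five are patient pain, patient global, physician global, HAQ and an acute phase reactant.

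**HAQ on day 2.** Section 6.7 states: "Complete efficacy and safety assessments will be made on Days 1 (baseline), 2, 5b, 10, and 15". Its sequence of assessments begins with "Patient reported assessments: patient's global assessment of disease activity (VAS), pain (VAS), HAQ". In Figure 1 the HAQ row is marked on day 1, at both day 5 visits (5 and 5b), and on days 10 and 15. It is blank on days 2, 3 and 4. Item 9 of section 9.3.3 analyses "The change in HAQ scores from baseline to day 5, 10 and 15", without day 2.

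**Joints.** Section 6.7.1 states: "An assessment of 28 joints for swelling and tenderness will be made". The matching row of Figure 1 is labelled "DAS28 (with 66/68") for visits 0 to 4, with the same 66/68 note for the later visits. Section 9.3.1 gives no number of joints for the ACR counts.

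**Missing data.** Section 9.4 replaces missing values by the last observed value.

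**The concern.** The data collection schedule and the list of analyses do not match. A study nurse working from Figure 1 will not hand out the HAQ on day 2; one working from section 6.7 will. In the first case item 3 has a component with no data on day 2, and item 4 applies a harder rule on day 2 than on the later days under the same endpoint name.

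The joint count raises a similar problem at every visit, because improvement in both counts is compulsory for ACR response. An assessor reading section 6.7.1 alone examines 28 joints; one reading Figure 1 examines 66/68. The two could classify the same patient differently.

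Both are questions of what is recorded at the visit. A later analysis plan can choose how to score what was collected, but it cannot recover a questionnaire that was not given or joints that were not examined.

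**Working it through.** The protocol gives no figure of its own on this point, so there is none to reproduce. The sample size in section 9.1 concerns DAS28 and plays no part here.

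**Step 1: the day 2 HAQ, place by place.**

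| Place in the protocol | Day 2 HAQ |
|---|---|
| 6.7 | collected, as part of a complete assessment |
| Figure 1 | not collected |
| 9.3.3 item 9 | not analysed |
| 9.3.3 item 3 | needed, as a core-set measure |
| 9.3.3 item 4 with 9.3.1 | used, as one of five items |

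Section 6.7 with items 3 and 4 points one way, and Figure 1 with item 9 the other.

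**Step 2: what is left on day 2 under Figure 1.** The joint assessment, the three VAS scales and CRP/ESR are all marked on day 2. So both joint counts and four of the five further items exist, and only HAQ is absent.

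**Step 3: item 3.** With no day 2 HAQ there is nothing to analyse. If last observation carried forward is applied literally, day 2 HAQ equals baseline HAQ and the change is 0 for every patient. The ANCOVA of section 9.3.2 then regresses baseline on itself: the treatment coefficient is 0, the residual variance is 0, and no test is possible.

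**Step 4: item 4.** HAQ can never count as improved on day 2, so the rule becomes at least 3 of 4. Suppose each item improves independently with probability p. The protocol gives no value, so p is an assumption. Conditional on both joint counts having improved:

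- P(at least 3 of 5) = 10p³(1−p)² + 5p⁴(1−p) + p⁵
- P(at least 3 of 4) = 4p³(1−p) + p⁴

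For p = 0.3 the first is 0.1323 + 0.0284 + 0.0024 = 0.163 and the second is 0.0756 + 0.0081 = 0.084.

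| p | 3 of 5 | 3 of 4 | ratio | reduction |
|---|---|---|---|---|
| 0.3 | 0.163 | 0.084 | 0.513 | 49% |
| 0.4 | 0.317 | 0.179 | 0.565 | 44% |
| 0.5 | 0.500 | 0.312 | 0.625 | 38% |

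**Step 5: correlated items.** Section 9.3.3 itself calls the secondary variables highly correlated, so independence is the extreme case. The same comparison was simulated with a one-factor Gaussian model, 400,000 draws per setting, with assumed latent correlation ρ:

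| ρ | p | 3 of 5 | 3 of 4 | reduction |
|---|---|---|---|---|
| 0.3 | 0.2 | 0.116 | 0.071 | 39% |
| 0.3 | 0.4 | 0.360 | 0.249 | 31% |
| 0.3 | 0.6 | 0.641 | 0.505 | 21% |
| 0.6 | 0.2 | 0.160 | 0.116 | 27% |
| 0.6 | 0.4 | 0.382 | 0.305 | 20% |
| 0.6 | 0.6 | 0.618 | 0.532 | 14% |
| 0.8 | 0.2 | 0.182 | 0.148 | 18% |
| 0.8 | 0.4 | 0.392 | 0.339 | 13% |
| 0.8 | 0.6 | 0.608 | 0.551 | 9% |

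The reduction runs from 9% to 39%.

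**Step 6: joints.** The DAS28 formula in section 6.4.1 needs only the 28 joints listed there. The only evident use in this protocol for a 66/68 examination is therefore ACR response, yet section 9.3.1 does not say so.

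**The case against.** A reader might infer that ACR results cannot be scored at all under the protocol's own definition. The documents do not support that. On day 2 four of the five items are scheduled, so three improved items remain attainable. On days 5b, 10 and 15 HAQ is scheduled and all five are available. Because section 9.3.1 names no joint number, the 28 versus 66/68 conflict leaves the count undefined without making scoring impossible.

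A reader might also infer a biased treatment comparison. Item 4 compares the arms visit by visit, and the missing HAQ affects both blinded arms by the same rule, so neither is favoured. What remains is a stricter day 2 criterion with less sensitivity, and a response series that is not like for like over time.

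Three further points carry weight:

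- Section 9.4 speaks of missing data and does not say that a measurement never scheduled counts as missing. The zero HAQ change follows only from a literal reading; on the other reading there is simply nothing to analyse.
- Section 6.7.1 says its assessments follow Figure 1, and a 66/68 examination includes the 28 joints. Losing the wider counts is a risk, not a foregone outcome.
- Figure 1 and item 9 agree with each other, so the day 2 omission may be deliberate and section 6.7 the loose sentence. The protocol does not settle this, so the correction should leave the choice to the sponsor.

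None of this removes the contradiction between sections 6.7 and 9.3.3 (items 3 and 4) on one side and Figure 1 and item 9 on the other.

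**Conclusion.** The point holds as an internal inconsistency affecting secondary endpoints. If Figure 1 is followed, the day 2 HAQ component of item 3 cannot be analysed, and day 2 ACR response rests on 3 of 4 items where days 5b, 10 and 15 use 3 of 5.

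The 38-49% reduction rests on independent items with assumed p of 0.3 to 0.5. The 9-39% range rests on assumed latent correlations of 0.3 to 0.8 and p of 0.2 to 0.6, and is closer to what the protocol says about its variables. Both apply only once the two joint counts have improved, so they are not differences in overall ACR response rates.

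The joint count used for ACR is unspecified at all visits, and the text and the schedule differ on what is examined. The primary endpoint, DAS28CRP at day 5b, uses 28 joints and no HAQ, and is unaffected. The correction should be made because it is cheap and uncollected data cannot be recovered.

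**What to change.** Reconcile the day 2 HAQ in one of two ways:

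1. Add HAQ to visit 2 in Figure 1 and add day 2 to item 9. The cost is one 20-question form at a visit that patients already attend.
2. Delete day 2 from item 4 and from the HAQ component of item 3, and correct section 6.7 so that day 2 is not described as a complete assessment. Section 9.3.1, which has ACR response calculated at each visit, should be limited to match. The cost is one early time point of a secondary endpoint.

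On joints, align section 6.7.1 with Figure 1 on which joints are examined. State in section 9.3.1 which count ACR response uses, and that DAS28 uses the 28-joint subset. This is a wording change. Neither correction alters the sample size or the primary analysis.
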